#### Training and fidelity monitoring

All the clinicians involved will attend a 1-day NECT training session, delivered by the creators of the program ([name], [name]). Training will include discussion and role-playing exercises, with corrective feedback from the trainers. Regular group supervisions will be organized to ensure treatment fidelity. NECT fidelity will be monitored using the NECT Fidelity Scale, developed by [name] et al. [34].

#### The experimental intervention

The French adaptation of NECT is a manualized, structured, 12-session, group-based intervention conducted by two facilitators. The number of sessions was reduced in the French adaptation and their duration extended to match the typical duration of psychosocial interventions in French-speaking countries (up to 15 sessions). Figure 4 provides an overview of the NECT topics. The 2-h sessions are divided into three main parts: (1) psychoeducation about stigma, self-stigma and myths about mental disorders; (2) cognitive restructuring targeting negative thoughts about the self and dysfunctional attitudes and (3) story-telling exercises in which participants tell stories about themselves, receive feedback from other group members and facilitators and are invited to apply the cognitive restructuring skills learnt in the previous sessions to their personal life narratives. At-home practice exercises are carried out between the sessions.

**Fig. 4 Fig4:**
[figure not shown]
Structure of NECT topics

### The control condition

The control condition refers to the group receiving current standard care during the first 6 months of the study before attending NECT after T1. There is no definition of standard care. The association of pharmacological treatment with psychiatric rehabilitation is however recommended in all the international guidelines on SMI [49–51]. All participants will attend day-care recovery-oriented services offering several forms of psychiatric rehabilitation (group CBT on positive symptoms, general psychoeducation, cognitive remediation, vocational rehabilitation, supported employment). Information about the interventions received during the follow-up period (with their duration and the number of sessions) will be systematically collected by the clinical research officer and taken into account when analysing the results.

### Assessments

At baseline and at follow-up, socio-demographic and illness-related information (education level, employment and marital status, psychiatric diagnosis, age of onset, illness duration, current pharmacological treatment) will be collected. All outcome measures listed below are part of routine clinical evaluations in the national REHABase and FACE networks for SZ and BD [36, 42, 43] approved by the relevant ethical committees.

#### Primary outcome

Social function will be assessed with the Personal and Social Performance Scale [44] (PSP), a clinician-reported measure of social dysfunction using six-point severity scale in four life domains (socially useful activities, personal and social relationships, self-care and disturbing or aggressive behaviours). PSP provides an overall rating score ranging from 1 to 100, higher scores representing better personal and social functioning. PSP showed acceptable internal consistency [52], excellent inter-rater reliability [53] and a satisfactory ability to detect changes [44]. A seven-point improvement during clinical trials is considered to be clinically significant [44].

#### Secondary outcomes

Self-stigma will be assessed using the Internalized Stigma of Mental Illness scale (ISMI [2, 54]), a 29-item self-report measure designed to assess a person’s personal experience of stigma related to mental disorders and is rated on a four-point Likert scale. Items are summed to provide a mean total score and five subscale scores (alienation or feeling of being a devalued member of the society; stereotype endorsement or agreement with the negative attitudes about SMI; discrimination experience; social withdrawal as a coping strategy and stigma resistance). Stigma resistance is generally excluded because of poor correlations with other subscales [32, 34]. Higher scores reflect higher levels of self-stigma. Scores above 2.5 indicate moderate to high levels of self-stigma [2, 3]. Illness severity will be assessed in patients with SZ using the Positive and Negative Syndrome [55] (PANSS) scales. Current depressive symptoms were evaluated using the Montgomery-Asberg Depression Rating Scale [56] (MADRS) and current manic symptoms with the Young Mania Rating Scale [57] (YMRS). Insight and treatment adherence will be assessed with self-reported measures (Birchwood Insight Scale (BIS) [58]; Medication Adherence Rating Scale (MARS) [59]). Quality of life will be evaluated with the self-reported Subjective Quality of Life scale [60] (S-QoL) and wellbeing using the Warwick-Edinburgh Mental Well-being Scale [61] (WEMBS). Self-esteem will be measured with the Self-Esteem Rating Scale [62] (SERS) and personal recovery using the self-reported Stage of Recovery Instrument [63] (STORI). Baseline neuropsychological cognitive assessments include Wechsler Adult Intelligence Scale-4th edition [64] (WAIS-IV) subscales assessing working memory, verbal abstraction and hypothetico-deductive reasoning, BEM-144 story subtest for auditive-verbal memory [65], Trail Making Test A and B (TMT-A or B) [66] respectively for speed of processing and reactive mental flexibility, D2-R for selective attention, concentration and speed of processing [67], and shopping test for planning abilities [68]. Theory of mind will be assessed at baseline using the Versailles-Situational Intention Reading Test [69] (V-SIR).

### Statistical analysis

Intention-to-treat analyses will be conducted in the first instance. The analyses will be conducted using parametric tests for normal distributed data (Student’s *t* and covariance analysis with repeat measures ANCOVA) and with non-parametric tests (Mann-Whitney *U* and Kruskal-Wallis test) in case of significant deviations from the normal distribution. The primary analysis was done by intention to treat.

We will analyse all outcomes using multilevel regression models with time point and intervention status as fixed effects and clusters as a random effect. Timepoint will be included as a categorical variable [39]. The statistical analysis will be done using the R software, version 3.2.3 [70]. The psych package version 1.5.8 will be used [71]. Effect size (Cohen’s *d*) will be calculated using the effsize package [71]. Size effects inferior to 0.20 will be considered as negligible, from 0.20 to 0.40 as small, from 0.40 to 0.60 as moderate and superior to 0.60 as strong [71]. The leaps package version 2.9 will be used for variable selection [72]. The level of confidence intervals will be set at 0.95 and the significance level of tests at 0.05.

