## Methods and design

### Design

This stepped wedge cluster randomized controlled study is multi-centric, prospective, interventional and exploratory. For ethical purposes, we have chosen a stepped wedge cluster randomized trial design, with a waiting list type control condition. Previous research from the French national REHABase network showed that (i) most patients were dissatisfied with their interpersonal relationships at the time of admission and asked for interventions improving social function [36] and (ii) elevated self-stigma was frequent (31.2% of the 738 participants [37]) and was negatively associated with recovery-related outcomes. Self-stigma has been negatively associated with patient’s longitudinal outcomes and to lower benefits from psychiatric rehabilitation [38]. Providing NECT to all participants aims at not excluding participants from interventions improving social function (e.g. social skills training or social-cognitive remediation) during the follow-up period without proposing them a credible therapeutic alternative (i.e. self-stigma reduction). This also aims at reducing potential deception bias and dropouts in participants allocated to the control group. Each centre will represent a cluster. In stepped-wedge RCTs, all clusters are evaluated before and after providing the intervention and each cluster switches from control to become exposed, but not at the same point in time [39, 40]. The 12 centres participating to the study will be randomized into two groups: one group (group 1) receiving the intervention at the beginning of the study (T0) and one group (group 2) being a control group for the first 6 months and receiving the intervention after (T1). The stepped-wedge design of this 2-group trial can be seen on Fig. 1.

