#### Recruitment and randomization

Patients diagnosed with schizophrenia, bipolar disorder or borderline personality disorder (DSM-5 criteria [41]) will be recruited through six Rehabase psychiatric rehabilitation network centres [36], three FondaMental Academic Centres of Expertise (FACE) for SZ or BD [42, 43], one unit specialized in mood disorders at the Geneva university hospital, one psychiatric day-care clinic specialized in mood and personality disorders in Grenoble and one psychiatric rehabilitation centre located in the psychiatric hospital in Caen. The selected sites are already actively involved in treating patients with SZ, BD or BPD and have previous research experience in the field of psychiatric rehabilitation. Regular group meetings will be organized to monitor quality control and ensure good inter-rater reliability. A list of eligible participants will be generated under the supervision of the coordinating centre clinical research officer. Each eligible patient will be approached by a trained member of the research team and invited to participate in the study, thereby eliminating selection biases. Eligible patients will be given a leaflet describing the program and the research. Informed consent will be taken during a medical interview with one of the investigators. The clinical research officer of the coordinating centre (Grenoble) will be in charge of the randomization process for participants from all centres. Clusters will be randomized to receive the intervention at either T0 or T1. Stratified randomization will be used to ensure that cluster types are well balanced across groups. Outcomes will be compared in all groups at T0 and T1 (duration of intervention= 6 months). Six-month and 12-month outcomes for groups 1 and 2 will be measured at T2 (18 months after T0) to evaluate the stability of the effects over time. A 7-point improvement in social functioning measured using Personal and Social Performance Scale [44] (PSP) is generally considered as clinically significant. We plan to include 5 patients per centre and per group, meaning that there will be 10 participants included per centre for a total of 120 patients included (60 in group 1, 60 in group 2). This sample size was calculated using R package ‘pwr’ [45] based on Cohen [46] (*d* = 0.50, alpha level of 0.05) without allowing for intra-cluster correlations and the cluster and time effects found in stepped-wedge designs [47, 48]. This could be a considerable limitation, as it might have underpowered the trial [47]. Most of the outcome measures are self-rated questionnaires; the other evaluations will be conducted by an evaluator who has not taken part in the intervention. The schedule of enrolment, interventions and assessments is shown in Fig. 3 (SPIRIT diagram).

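### The plan gives patient-level tests and a cluster multilevel model side by side without ranking them; the t and rank tests would not hold the 0.05 level at any positive intra-cluster correlation

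*Protocol article*

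**What the plan says.** **Unit of randomisation.** The Design section states "Each centre will represent a cluster" and "The 12 centres participating to the study will be randomized into two groups". Recruitment and randomization repeats it: "Clusters will be randomized to receive the intervention at either T0 or T1". The allocation is therefore by whole centre.

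**First family of analyses.** Statistical analysis begins "The analyses will be conducted using parametric tests for normal distributed data", naming Student's t and repeated-measures ANCOVA. It moves to Mann-Whitney U and Kruskal-Wallis "in case of significant deviations from the normal distribution". No centre term is mentioned for any of these.

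**Second family.** The next paragraph states "We will analyse all outcomes using multilevel regression models with time point and intervention status as fixed effects and clusters as a random effect".

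**Ranking.** None is given. The term primary analysis occurs once in the section, in a sentence about intention to treat that follows the simple tests and names no model. The significance level is 0.05 throughout.

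**The concern.** A reader of the section cannot tell which analysis decides whether the intervention improved PSP. One route respects the randomisation by centre. The other, if followed as written with a t or rank test, does not, and a normality check picks the test within it. Two consequences follow.

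- The deciding test can be settled after the data are seen, by choosing a paragraph or by the outcome of the normality check.
- On the patient-level route, the stated 0.05 is not the real false-positive rate once patients in the same centre resemble each other.

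Some resemblance is plausible here. The sites differ in kind (rehabilitation centres, expert centres, a mood-disorder unit, a day clinic), standard care is left undefined, and PSP is rated by clinicians.

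This is a matter of what the text states, not of detail left to a statistical analysis plan: both families are positively prescribed.

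**Working it through.** **Inputs**

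- 12 centres, each a cluster (Design).
- Patients per centre: "We plan to include 5 patients per centre and per group, meaning that there will be 10 participants included per centre" (Recruitment and randomization).
- Group size: the same section plans 60 in each group, 120 overall. With whole centres allocated, 60 / 10 = 6 centres per group.
- Significance level 0.05 (Statistical analysis); two-sided is assumed, as the article does not say.
- ICC: not given. Assumed range 0.01 to 0.10.

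**Step 1. The plan's own figure.** With ICC = 0 and no true effect, simulation of 6 v 6 centres of 10 gives rejection rates of 5.0% (t), 4.9% (Mann-Whitney) and 5.3% (Kruskal-Wallis). The nominal 5% is therefore recovered when there is no clustering.

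**Step 2. Formula for a test that ignores centre.**

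Design effect DE = 1 + (10 − 1) × ICC

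True type I error = 2 × [1 − Φ(1.96 / √DE)]

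- ICC 0.01: DE = 1.09; 1.96 / √1.09 = 1.877; error 6.0%
- ICC 0.02: DE = 1.18; 1.96 / √1.18 = 1.804; error 7.1%
- ICC 0.05: DE = 1.45; 1.96 / √1.45 = 1.628; error 10.4%
- ICC 0.10: DE = 1.90; 1.96 / √1.90 = 1.422; error 15.5%

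**Step 3. Check by simulation, no true effect** (20,000 runs; Kruskal-Wallis 3,000)

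| ICC | t | Mann-Whitney | Kruskal-Wallis | t on the 12 centre means |
|---|---|---|---|---|
| 0.01 | 6.0% | 5.9% | 5.7% | 5.0% |
| 0.02 | 6.9% | 7.0% | 6.9% | 5.0% |
| 0.05 | 10.7% | 10.4% | 9.9% | 4.9% |
| 0.10 | 15.5% | 15.0% | 15.4% | 5.0% |

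The rank tests give no protection, because the problem is dependence and not distributional shape. A test on centre means stays at about 5%.

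**Step 4. ANCOVA of T1 on T0 with no centre term** (10,000 runs). This needs two further assumptions: a within-person correlation of 0.6, and a cluster autocorrelation, that is, the share of the centre effect that is the same at T0 and T1.

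| ICC | autocorrelation 0.5 | 0.8 | 1.0 |
|---|---|---|---|
| 0.01 | 6.3% | 5.3% | 5.0% |
| 0.05 | 11.0% | 8.9% | 6.3% |
| 0.10 | 17.0% | 12.2% | 7.5% |

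Baseline adjustment removes much of the inflation when centre effects are largely stable, and nearly all of it when they are also small. When only half the centre effect is stable, the error is about the same as for the t test or slightly higher.

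**The case against.** **The multilevel sentence may be meant to govern.** It alone refers to all outcomes and names intervention status, time and cluster. Kruskal-Wallis adds nothing to Mann-Whitney for two groups, so the first paragraph may also be meant for other comparisons, such as between diagnoses. This is a reasonable reading, but the text does not state that limit. The ambiguity stands. What is not shown is that a patient-level test will decide the trial.

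**A reader might infer that there are two conflicting primary analyses.** The article calls neither family primary. Competing and unranked is as far as the text goes.

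**A reader might infer that the false-positive rate simply exceeds 5%.** That needs two conditions: a first-paragraph test is used for the between-group comparison, and the ICC is above zero. At an ICC of 0.01 the excess is about one percentage point.

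**A reader might infer that every test in the first paragraph ignores centre.** That is true of the t and rank tests as named. For ANCOVA the article does not say whether centre would enter, and Step 4 applies only if it does not.

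**A reader might extend the criticism to the confidence interval of Cohen's d.** The article says that d will be calculated with a named package. It does not say that an interval for d from that package will be reported, so this has no basis in the text.

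**Five patients per centre and per group.** Read literally, this splits each centre across both groups, and ignoring centre would then be conservative. It conflicts with the statements that whole centres are randomised, which are repeated and explicit. The calculation follows those, with 10 patients per centre in one group.

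**Conclusion.** The point holds in a conditional form. The article prescribes two unranked families of analysis, and one of them contains tests that do not match randomisation by centre. If the t or rank tests are used to compare groups on PSP or a secondary outcome, the 0.05 level is not held at any positive ICC. The true error is about 6%, 7%, 10% and 16% at assumed ICCs of 0.01, 0.02, 0.05 and 0.10, with 6 v 6 centres of 10 patients and two-sided testing. For ANCOVA without centre, the figure runs from 5.0% to 17.0% across the assumed ICCs and degrees of stability.

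The authors acknowledge under Recruitment and randomization that the sample size ignored intra-cluster correlation. No such acknowledgement covers the simple tests. The matter should be settled before analysis, because the conclusion on the primary outcome could turn on which paragraph is followed.

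**What to change.** 1. State that the multilevel model with centre as a random effect is the sole confirmatory analysis of PSP and of between-group secondary outcomes. Name a small-sample correction suited to 12 clusters, for example Kenward-Roger or Satterthwaite degrees of freedom.
2. Remove the sentence on t, ANCOVA, Mann-Whitney and Kruskal-Wallis tests for those comparisons, or limit it to descriptive use.
3. State that no normality test will choose the analysis.
4. If a distribution-free check is wanted, pre-specify it as a sensitivity analysis that is run whatever the residuals look like: a permutation test over the centre allocations that the stratified randomisation permits. Without stratification there would be 12! / (6! × 6!) = 924 equal splits; stratification by cluster type leaves fewer, so the permitted set should be listed. Making this test conditional on non-normal residuals would bring back the data-driven choice that item 3 removes.

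The cost is wording, plus a few lines of code if the permutation test is added. No change to recruitment, visits or data collection is needed, and the Trial status section says that the trial had not begun when the article was written.

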**Methods:**

This is a 12-centre stepped-wedge cluster randomized controlled trial of NECT effectiveness on social functioning in SMI, compared to treatment as usual. One hundred and twenty participants diagnosed with schizophrenia, bipolar disorder or borderline personality disorder will be recruited across the 12 sites. The 12 centres participating to the study will be randomized into two groups: one group (group 1) receiving the intervention at the beginning of the study (T0) and one group (group 2) being a control group for the first 6 months and receiving the intervention after (T1). Outcomes will be compared in both groups at T0 and T1, and 6-month and 12-month outcomes for groups 1 and 2 will be measured without a control group at T2 (to evaluate the stability of the effects over time). Evaluations will be conducted by assessors blind to treatment allocation. The primary outcome is personal and social performance compared across randomization groups. Secondary outcomes include self-stigma, self-esteem, wellbeing, quality of life, illness severity, depressive symptoms and personal recovery.

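### The multilevel model gives a random effect to centre only, although each patient is measured repeatedly; the test of NECT is conservative and loses power

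*Protocol article*

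**What the plan says.** The Statistical analysis section sets one model for every outcome: "We will analyse all outcomes using multilevel regression models with time point and intervention status as fixed effects and clusters as a random effect". It adds: "Timepoint will be included as a categorical variable". The Design section defines the cluster: "Each centre will represent a cluster". No term for the patient appears in this model.

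The same section also lists t tests, "covariance analysis with repeat measures ANCOVA" and non-parametric tests. It does not say how these relate to the multilevel model or which analysis is primary.

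On timing, the abstract says "Outcomes will be compared in both groups at T0 and T1" and describes T2 as having no control group. Recruitment and randomization gives 10 participants per centre and 120 in all ("60 in group 1, 60 in group 2"). The objectives include whether effects persist at later follow-up, which implies that the same patients are followed.

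**The concern.** In a closed cohort, two PSP scores from one patient are more alike than scores from two patients at the same centre. A model with a centre effect alone cannot represent this. It moves most of the between-patient variance into the residual and charges it to the comparison over time that identifies the NECT effect. The baseline score of each patient is collected but mostly not used to sharpen that comparison.

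At stake is whether a real benefit on PSP is missed. The article already concedes that its sample size, computed without clustering or time effects, may leave the trial underpowered. The same model is stated for all secondary outcomes.

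**Working it through.** **The plan's own figure.** The article gives d = 0.50, alpha 0.05 and 60 per group, but no power. For independent patients at one visit, two-sided, normal approximation: 0.5 × √(60/2) − 1.96 = 0.779, so power is 78%. No power is stated, so 120 can be neither confirmed nor refuted.

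**Inputs.** From the article: 12 centres, 10 patients each, d = 0.5, alpha 0.05. Assumed: 6 centres per group, two-sided testing, no dropout, total SD 1, ICC 0.05, within-patient correlation 0.6. The variance then splits into centre 0.05, patient 0.55 and residual 0.40.

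**Step 1: what the centre-only model estimates.** Expected REML values are residual 0.925 and centre 0.077. A moment check comes close:
- residual: (12 × 20 × (0.95 − 0.075) − 0.8) / 226 = 0.926
- centre: 0.125 − 0.926/20 = 0.079

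Here 0.075 = 0.55/10 + 0.40/20, and 0.125 = 0.05 + 0.075. The fitted residual is more than twice the true 0.40, because it has absorbed the patient variance.

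**Step 2: reported standard error, T0/T1.** With time and intervention status as fixed effects, the estimator is the T1 group difference minus w times the T0 group difference. The model's variance of a centre mean at one visit is v = 0.0925 + 0.077 = 0.1695, and w = 0.077/0.1695 = 0.454. Reported variance = (1/6 + 1/6) × v × (1 − w²) = 0.0448, so SE = **0.212**.

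**Step 3: true standard error of that estimator.** True variance of a centre mean: V = 0.05 + 0.95/10 = 0.145. Covariance between visits: C = 0.05 + 0.55/10 = 0.105. True variance = (1/3) × [V(1 + w²) − 2wC] = 0.0265, so SE = **0.163**. The ratio is 0.2119/0.1627 = 1.30.

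**Step 4: alpha and power as written.** The rejection limit is 1.96 × 0.2119 = 0.415. Under the null, 0.415/0.1627 = 2.55, so two-sided alpha is about 0.011. At d = 0.5, (0.5 − 0.415)/0.1627 = 0.52, so power is about 70%.

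**Step 5: with a patient effect.** The best weight is C/V = 0.724. Variance = (1/3) × 0.145 × (1 − 0.724²) = 0.0230, so SE = 0.152. Power is 91% with a normal reference and 84% with t on 10 df. Most of the loss in Step 4 comes from the overstated standard error (0.212 against 0.163), less from the estimator itself (0.163 against 0.152).

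**Range.** For ICC 0.02–0.10 and correlation 0.4–0.8, with no drift of centre means over time, the T0/T1 standard error is about 15–62% too large.

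**Step 6: an unfavourable case for the fix.** Take ICC 0.10, correlation 0.4 and centre drift (cluster autocorrelation 0.8). Then V = 0.10 + 0.90/10 = 0.19 and C = 0.08 + 0.03 = 0.11. The written model reports 0.214 against a true 0.205: 4% too large, alpha about 0.04, power 65%. With the right covariance, SE = √[(1/3) × 0.19 × (1 − (0.11/0.19)²)] = 0.205, and power with t on 10 df is about 60%.

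**Step 7: baseline-adjusted PSP at T1.** Take ICC 0.10, correlation 0.5, no drift. The individual-level slope is b = 0.40/0.90 = 0.444, V = 0.19 and C = 0.14. Variance = (1/3) × [V(1 + b²) − 2bC] = 0.0344, so SE = 0.185 and power with 10 df is about 68%, against 67% as written. Over ICC 0.02–0.10 and correlation 0.5–0.7, this analysis gives about 68–92%.

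**The case against.** The strongest reply is that the error is on the safe side. That stands. A reader who sees a misspecified random-effects structure might infer inflated false positives; in every scenario computed the reported standard error was too large, so the written model cannot manufacture a claim of efficacy in this way. The article also calls the trial exploratory and admits possible underpowering. But that admission concerns clustering and time effects in the sample size, not repeated measures in the analysis model.

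A second reply is that the repeated-measures ANCOVA covers the within-patient correlation. It may, but as named it has no centre term and is not tied to the multilevel model. Neither named method is stated to handle both levels.

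Third, the detail could be left to an analysis plan. That holds for the reference distribution: a reader might infer that small-sample inference for 12 centres has been rejected, but the article is only silent on it, and this is no defect. It does not hold for the random effects, which the article states.

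Fourth, three-visit figures look more dramatic: at ICC 0.05 and correlation 0.6, power is 77% against 95% (normal). They should not lead, because T2 has no control group and they assume one constant effect carried to T2.

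**Conclusion.** The concern holds as a loss of power. The stated model does not fit a design in which the same patients are measured repeatedly, and its intervals for the NECT effect are wider than their nominal 95% level warrants. In the base case the T0/T1 standard error is 30% too large and power is about 70%, where a patient effect would give about 84–91%.

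The size rests on an assumed ICC and within-patient correlation. It also rests on an assumed layout: the article's statement of five patients per centre and per group does not sit well with whole centres being randomised. The direction did not change over the values tried, with or without centre drift, but the overstatement fell to about 4% in the least favourable case.

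A reader might also infer that correcting the model always raises power. The calculations do not support that: with about 10 df, low within-patient correlation and centre drift, the gain can vanish or reverse slightly (65% to 60% in Step 6). What the correction gives in that case is coverage close to nominal.

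**What to change.** Add a random intercept for participant nested in centre to the multilevel model. Alternatively, analyse PSP at T1 adjusted for baseline PSP with a random centre intercept. State which analysis is primary, and say how the repeated-measures ANCOVA relates to it or remove it.

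When the patient term is added, also use small-sample degrees of freedom suited to 12 centres (Kenward-Roger, or t with at most 10 df) and a centre-by-time random effect. These belong with the correction: in simulations with centre drift, a patient effect alone with a normal reference gave 6–15% type I error, which would replace a conservative test with an anti-conservative one.

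The cost is a few lines of model specification and no extra patients or visits. The critical value rises from 1.96 to about 2.23, with the downside on power noted above. The article reports that recruitment had not begun, so the change could be made before any data are seen.
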